### Assignment of interventions

#### Patient randomisation

Patients are randomly assigned to the treatment groups (liposuction or CDT alone) centrally using the 24/7 Internet randomisation service ALEA (FormsVision BV, Abcoude, NL) in a 2:1 ratio (liposuction: CDT alone) based on permuted blocks of varying length as provided by ALEA using a pseudo-random number generator. Assignment is stratified by stage of lipedema and trial site. The randomisation service is set up and maintained by the Institute of Medical Statistics and Computational Biology, University of Cologne. Programming (using a web-interface) and validation of the service are done according to the Institute’s SOPs. The assignment of the groups can be made by all investigators, except the investigator (blinded investigator) carrying out the clinical assessments and questionnaires after surgery who should not be aware of who is receiving liposuction or CDT. The randomisation sequence is concealed from all clinical staff, i.e. only ALEA service administrators have access to the sequence.

#### Blinding (masking)

This study is a single-blind (investigator-blinded) trial. After randomisation, all examinations will be conducted by an investigator who will be blinded to the treatment allocation. Therefore, the surgical scars are taped by unblinded study personnel before each visit (dummy patches in the control group) and patients are asked not to disclose the received therapy to the blinded investigator. The blinded examination of the patient must not be performed by a surgeon or an unblinded investigator. The blinded investigator is not allowed to access the database and is informed that he is not allowed to view the patient’s file of the patient he is examining (except in an emergency). The data collected by the blinded investigator are documented on working sheets and entered into the eCRF by unblinded study personnel in a timely manner.

The analysing statistician will also be kept masked to treatment assignment until the final statistical analysis is completed.

### Data collection, management, and analyses

#### Data collection and management

The IT infrastructure and data management are provided by the Clinical Trials Centre Cologne (CTCC).

The trial database is developed and validated by CTCC on the basis of standard operating procedures. All changes made to the data will be documented in an audit trail. The commercial online software TrialMaster^TM^ (Anjusoftware.com) is used as a data management system, ensuring data safety by a firewall and backup system and including multiple data storage sites. The data are backed up daily.

All relevant trial data collected during the trial are documented soon after data gaining and entered into the eCRF by the responsible investigators or a person authorised by the principal investigator (exception of the blinded investigator).

This includes all outcomes measures and questionnaires. Automatic plausibility checks are run during data entry to immediately detect discrepancies. Data management of the CTCC carries out checks on the completeness and plausibility of the study data and clarifies all queries with the study centre electronically via the trial software. These queries must be answered promptly by the study centre. The eCRFs are signed by the principal investigator at the end of a patient’s trial participation to confirm the accuracy of the data. After completion and cleaning of the data, the database is closed and the data will be exported for statistical analysis.

To monitor risks and ensure the data quality of the trial, a central quality control process (CQC) is set up.

Using CQC, the performance of the trial sites indicating the documentation rate, documentation quality, and recruitment rate will be evaluated. In the case of conspicuous data (e.g. incorrect or insufficient documentation), this quality control process allows for early intervention and correction of errors.

#### Data protection

The provisions of the EU data protection basic regulation and data protection laws including their national implementation in Germany are observed. It is ensured that all investigational materials and data are pseudonymised in accordance with data protection regulations before scientific processing.

Patients will be informed that their pseudonymised data will be passed on in accordance with provisions for documentation and notification pursuant to § 12 and § 13 of the Good Clinical Practice (GCP) regulations to the recipients described there. Patients, who do not agree to the data handling as described in the informed consent, will not be included in the trial.

### Statistical methods

The primary analysis is according to the intention-to-treat. The primary outcome ‘success’ is evaluated by the stratified (by stage) Mantel-Haenszel test [25] at two-sided significance level of 5% (H_0_: odds ratio = 1 vs. H_A_: odds ratio ≠ 1). If this test is statistically significant, the equality of the success rates in the separate stages is evaluated by Fisher’s exact test (hierarchical test strategy). A missing primary outcome or change of the randomly assigned treatment is counted as failure. No interim analysis is planned. Secondary is the analysis of patients treated and observed per protocol (i.e. completed liposuction or ≥80% of planned CDT sessions done; valid primary outcome). Secondary and further outcomes are evaluated without adjusting for multiple hypothesis testing (i.e. no alpha correction is applied). Distributions of quantitative variables are described as mean (standard deviation) and percentiles (0, 25, 50, 75, 100), qualitative variables are summarised by count and percentage. The impact of missing outcome data is assessed by sensitivity analyses based on single/multiple imputation. The information on AEs is assessed (according to severity, intensity of symptoms, causal relationship to the CDT or intervention), coded and summarised by contingency tables. Subgroup analysis is done by patient age, study centre and surgeon.

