### Trial design

LIPLEG is a multicentre, controlled, randomised, investigator-blinded trial. Female patients with lipedema interested in participating in the trial could register in an online portal until the end of December 2019. The patients are randomly drawn and assigned to a trial site according to the nearest post code. Then, the patients will be contacted by the trial sites and assessed for eligibility by telephone interview. If the patient is assessed as eligible, a screening visit on-site will take place in order to check the inclusion and exclusion criteria. Patients will be considered for enrolment when all inclusion criteria are confirmed, and none of the exclusion criteria is fulfilled. Four hundred five patients are planned to be included in the trial and assigned in a ratio of 2:1 to treatment group A (liposuction) or B (CDT). The investigator assessing the primary and secondary outcomes will be blinded. The surgeon, patients and further investigators will not be blinded for the allocated treatment. Since lipedema mainly affects females, males will not be included in the study.

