## Methods

### Participants, interventions and outcomes

#### Study setting

The trial will be performed in > 10 trial sites in Germany, which are listed on ClinicalTrials.gov NCT04272827.

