### Sample size

#### Determination of trial size

According to the results of Schmeller et al. [22, 23], the success proportion of the intervention at each stage is expected to be at least 40% and that of the control to be at most 10%. The chi-square test requires 111 patients (74 vs. 37) per group to reach 80% power at two-sided significance level of 5% to detect such a difference. To compensate for the influence of dropouts and stratification, 135 patients per stage are included (this corresponds to an increase of approx. 20%). Accounting for up to 10% attrition from baseline to follow-up, the number of 450 patients is required in total.

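### Trial site is a randomisation stratum but not a stratum of the primary test, which stays valid but is conservative to the extent that site predicts success

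*Protocol article*

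**What the plan says.** The protocol article, under Patient randomisation, states: "Assignment is stratified by stage of lipedema and trial site". Allocation is 2:1 in permuted blocks of varying length. Under Study setting: "The trial will be performed in > 10 trial sites in Germany".

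Under Statistical methods, the primary outcome "is evaluated by the stratified (by stage) Mantel-Haenszel test" at a two-sided 5% level, with the null hypothesis written as an odds ratio of 1. The Abstract also names stage as the only stratifier. If the test is significant, Fisher's exact test follows in each stage. Site otherwise enters the analysis only as a subgroup variable (study centre and surgeon). No reason is given for leaving it out of the primary test.

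Determination of trial size plans for success in 40% or more on liposuction and 10% or less on CDT within every stage. It adds: "To compensate for the influence of dropouts and stratification, 135 patients per stage are included". Trial design gives the total: "Four hundred five patients are planned to be included in the trial".

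**The concern.** Blocking within stage and site balances the arms on site. If success rates differ between sites, that balance removes site differences from the treatment comparison. A test stratified by stage alone still counts them in its variance. The statistic is then too small on average, so the test rejects less often than 5% under the null and gives up some power under the alternative.

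The text makes some site effect plausible. Sites may be dermatology or plastic surgery units, run-in CDT follows the investigator's recommendation, and a missing outcome or a change of assigned treatment counts as failure, so site differences in retention feed directly into success.

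The pooled test also opens the stage-specific tests, so power lost there carries forward. And because odds ratios are not collapsible, a stage-only and a stage-by-site common odds ratio differ when site is prognostic. Which of them is reported should be fixed in advance.

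**Working it through.** **1. The plan's own figure.** For 40% vs 10% at 2:1, with r = 2 and pooled rate (0.1 + 2 × 0.4)/3 = 0.30, the control-arm size is

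n = [z(α/2)·√((1 + 1/r)·0.30·0.70) + z(β)·√(0.10·0.90 + 0.40·0.60/r)]² / 0.30²

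- 80% power, two-sided 5%: (1.960 × 0.5612 + 0.8416 × 0.4583)² / 0.09 = 24.5, so 25 vs 50, total 75. With continuity correction: 30 vs 60, total 90.
- 90% power with continuity correction: 37 vs 74, total 111.

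The stated 111 (74 vs 37) therefore does not follow from the stated 80% power. It matches 90% power with continuity correction. The same section also ends at 450 patients (405/0.9), while Trial design gives 405. Both are separate matters. They are noted here because the check below takes the 40% vs 10% effect and the 405 from these sections.

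**2. The two tests.** With N patients, T on liposuction, Y successes and A successes on liposuction in stratum k, the Mantel-Haenszel statistic without continuity correction is

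[Σ(A − TY/N)]² / Σ{T(N − T)·Y(N − Y) / [N²(N − 1)]}

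It was computed over the 3 stages and over stage by site.

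**3. Inputs.**
- From the protocol: 405 patients, 135 per stage, 2:1 allocation in permuted blocks within stage by site, more than 10 sites, two-sided 5%.
- Assumed: 11 sites (first set) or 12 sites (second set), unequal in size; blocks of 3 or 6; normal site effects on the logit scale, common to both arms, with SD 0, 0.5 or 1.0.
- Also assumed: every success rate other than 40% vs 10%.

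To read the SDs, take a 25% success rate, logit −1.10. SD 0.5 puts 95% of sites within −1.10 ± 0.98, about 11% to 47%. SD 1.0 puts them within −1.10 ± 1.96, about 4% to 70%.

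**4. Rejection rates (%).**

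| Success rates | Sites | Site SD | Stage only | Stage × site | Gain (points) |
|---|---|---|---|---|---|
| 30 vs 30 (null) | 11 | 0 | 4.52 | 4.74 | – |
| | | 0.5 | 4.38 | 5.06 | – |
| | | 1.0 | 3.42 | 4.76 | – |
| 25 vs 25 (null) | 12 | 0.5 | 4.6 | 5.1 | – |
| | | 1.0 | 3.7 | 5.0 | – |
| 40 vs 10 (planned) | 11 | 0, 0.5, 1.0 | 100 | 100 | 0 |
| 20 vs 10 | 11 | 0 | 74.84 | 74.56 | −0.28 |
| | | 0.5 | 76.32 | 77.28 | 0.96 |
| | | 1.0 | 74.00 | 77.80 | 3.80 |
| 40 vs 25 | 11 | 0 | 86.36 | 85.68 | −0.68 |
| | | 0.5 | 86.04 | 86.84 | 0.80 |
| | | 1.0 | 85.92 | 89.36 | 3.44 |
| 38 vs 25 | 12 | 0.5 | 72.8 | 74.3 | 1.5 |
| | | 1.0 | 63.0 | 68.7 | 5.7 |

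Simulated trials per 11-site setting: 5,000 under the null, 1,000 at the planned effect, 2,500 at the smaller effects. The 12-site settings used 4,000 each. The Monte Carlo standard error of a 5% rate is √(0.05 × 0.95/5,000) = 0.31 points, or 0.34 with 4,000 trials. For a power near 75% with 2,500 trials it is 0.87 points.

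**5. Stratum size.** With 11 sites there are 33 strata and 405/33 ≈ 12.3 patients in each, about 4 of them on CDT. At 10% success that is about 0.4 CDT successes per stratum. The simulated type I error of the stage-by-site test stays near 5% despite this sparseness.

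**The case against.** - **Stage-only strata fit the design.** The sample size is set per stage and the follow-up tests are per stage. The test is prespecified, valid, and errs on the safe side. This stands.
- **The harm is conditional.** The protocol gives no between-site variation. At SD 0 the two tests agree within simulation error. At SD 0.5 the stage-only type I error (4.4% and 4.6%) is hardly distinguishable from the 4.5% found with no site effect. Only SD 1.0 shows a clear effect, and a spread of about 4% to 70% between sites is large for specialised sites with experienced surgeons. This stands, and it limits the size of the point.
- **Surgeon and technique act only in the liposuction arm before the primary endpoint.** That is treatment-by-site variation, whereas the simulations use a site effect common to both arms. This also stands. The results speak to common influences such as case mix, CDT provision and retention.
- **Centre is already a planned subgroup.** True, but a subgroup analysis does not adjust the primary test.
- **The SAP may deal with it.** Supportive models are commonly left there. The strata of the primary test, however, are fixed in the protocol, so this is a stated choice and not an omission.

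A reader might infer from the mismatch that type I error is not controlled, or that the trial as planned loses power. The documents support neither: any error is on the conservative side, and at 40% vs 10% with 405 patients both tests reject in every simulated trial.

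**Conclusion.** The mismatch between randomisation strata and test strata is real, and its consequence is conditional and small. If site does not predict success, nothing is lost. A material loss needs both strong site differences (SD about 1.0) and an effect well below the planned one. It then amounts to about 3.5 to 6 power points, with a type I error of about 3.5% instead of 5%.

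The site SDs, the number and sizes of sites, the block lengths and the smaller effects are all assumptions. The point is still worth making because a smaller effect cannot be excluded: the Background itself says that randomised comparisons of surgical and conservative treatment are missing, and counting missing outcomes as failures can shrink the difference. This is a minor improvement, not a defect that threatens the trial.

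**What to change.** Before unblinding, specify the primary Mantel-Haenszel test and the Mantel-Haenszel common odds ratio over the randomisation strata (stage by site), and keep the stage-only test as a sensitivity analysis. If the stage-only test is to remain primary, give the reason for leaving site out and prespecify the stage-by-site test as the sensitivity analysis.

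The change is one of wording in the analysis plan and needs no new data. Its price is that strata with one arm only, or with no variation in outcome, carry no weight. In the simulations without a site effect this cost at most 0.7 power points, which is within simulation error. Covariate adjustment for pre-randomisation pain is a separate matter and is not needed here.

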#### Primary outcome

The primary outcome is the reduction of pain in the legs 12 months after completion of liposuction or after 12 months of treatment by CDT upon randomisation, respectively (≥ 2 points on a numerical rating scale with range 0–10; German pain questionnaire).

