##### Study visits and assessments

A screening visit (baseline visit) on site will be performed by the investigator including written informed consent, check of inclusion and exclusion criteria, and medical history. The following parameters are recorded on the screening visit as well as on the subsequent visits: weight, supplementary medications, leg circumference, occurrence of leg edema, haematoma tendency, validated questionnaires for the determination of pain (German pain questionnaire), quality of life (SF-36, DLQI, WHOQOL-BREF), depression (PHQ-9), overall impairment modified according to Schmeller [23] and functional limitations (LEFS). All patients will then receive CDT during a run-in phase of maximal 7 months. After randomisation, the patients receive either liposuction and CDT in the following observation period of 36 months or CDT alone. After 12 months of observation, patients of the CDT group can opt for liposuction surgery followed by another 24 months of observation. During the trial, physical activities are permitted as an optional adjuvant treatment for lipedema. The supportive use of a lymphomat is not permitted during the trial. Compliance of patients with the trial procedures will be monitored by questionnaires and clinical examination during each study visit. Visits and assessments are described in more detail in Tables 1 (liposuction group) and 2 (CDT group). A detailed trial flowchart is shown in Fig. 1.

**Table 1 Tab1:** Visit schedule—liposuction group

Liposuction group		Run-in phase				12 months of observation		24 months of follow-up			
Visit	Screening *Day 0*	P1 *≤4 wks*	P2 *6 mo. after P1*		Lipo-suction(s) *1–4 mo. after P2*	V1 *6 mo.*	V2 *12 mo.*	V3 *6 mo.*	V4 *12 mo.*	V5 *18 mo.*	V6 *24 mo.*
						*After completion of liposuctions(s)*		*After V2*			
Informed consent	x			**Liposuction of the legs (2–4 surgeries at intervals of 5–7 weeks)**							
Information about liposuction	x				x						
In-/exclusion criteria	x		x								
Demographic data	x										
Anamnesis	x										
Concomitant medication	x	x	x		x	x	x	x	x	x	x
Weight	x	x	x			x	x	x	x	x	x
Leg circumference	x	x	x			x	x	x	x	x	x
Leg oedema	x	x	x			x	x	x	x	x	x
Body fat	x	x	x			x	x	x	x	x	x
Leg volume (optional)	x	x	x			x	x	x	x	x	x
Arm circumference	x	x	x			x	x	x	x	x	x
Skin appearance	x	x	x			x	x	x	x	x	x
Quality of life (SF-36, DLQI, WHOQOL-BREF)	x	x	x			x	x	x	x	x	x
Depression (PHQ-9)	x	x	x			x	x	x	x	x	x
Hematoma (mod. to Schmeller et al. 2010)	x	x	x			x	x	x	x	x	x

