Overall impairment (mod. to Schmeller *et al*. 2010)	x	x	x			x	x	x	x	x	x
Pain (German Pain questionnaire)	x	x	x			x	x	x	x	x	x
Functional limitations (LEFS)	x	x	x			x	x	x	x	x	x
Randomisation			x								
ECG					x						
Laboratory data					x						
Pregnancy test	X		x		x						
Adverse events		x	x		x	x	x	x	x	x	x
Liposuction					x						
Query on the necessity of recurrent liposuction						x	x	x	x	x	x
Query on the scope of CDT	x	x	x		x	x	x	x	x	x	x

Abbreviations: *wks* weeks, *mo* months, *SF-36* Short Form 36, *DLQI* Dermatology Life Quality Index, *WHOQOL-BREF* World Health Organization Quality of Life-abbreviated version of the WHOQOL 100, *PHQ-9* Patient Health Questionnaire-9, *LEFS* Lower Extremity Functional Scale, *CDT* comprehensive decongestive therapy

**Table 2 Tab2:** Visit schedule—CDT group

CDT Group		Run-in phase		12 months of observation				24 months of follow-up			
Visit	Screening *Day 0*	P1 *≤4 wks.*	P2 *6 mo. after P1*	V1 *6 mo.*	V2 *12 mo.*		optional: Lipo-suction(s) 1-4 *mo. after V2*	V3 *6 mo.*	V4 *12 mo.*	V5 *18 mo.*	V6 *24 mo.*
				*After randomisation*				*After completion of liposuction(s) or V2*			
Informed consent	x					**On demand of the patient: liposuction of the legs (2–4 surgeries at intervals of 5–7 weeks)**					
Information about OP	x						x				
In-/exclusion criteria	x		x		x						
Demographic data	x										
Anamnesis	x										
Weight	x	x	x	x	x			x	x	x	x
Concomitant medication	x	x	x	x	x		x	x	x	x	x
Leg circumference	x	x	x	x	x			x	x	x	x
Leg oedema	x	x	x	x	x			x	x	x	x
Body fat	x	x	x	x	x			x	x	x	x
Leg volume (optional)	x	x	x	x	x			x	x	x	x
Arm circumference	x	x	x	x	x			x	x	x	x
Skin appearance°	x	x	x	x	x			x	x	x	x
Quality of life (SF-36, DLQI, WHOQOL-BREF)	x	x	x	x	x			x	x	x	x
Depression (PHQ-9)	x	x	x	x	x			x	x	x	x
Hematoma (mod. to Schmeller et al. 2010)	x	x	x	x	x			x	x	x	x
Overall impairment (mod. to Schmeller et al. 2010)	x	x	x	x	x			x	x	x	x
Pain (German Pain questionnaire)	x	x	x	x	x			x	x	x	x
Functional limitations (LEFS)	x	x	x	x	x			x	x	x	x
Randomisation			x								
ECG							x				
Laboratory data							x				
Pregnancy test	X				x		x				
Adverse events		x	x	x	x		x	x	x	x	x
Liposuction							x				
Query on the necessity of recurrent liposuction								x	x	x	x
Query on the scope of CDT	x	x	x	x	x		x	x	x	x	x

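### The primary analysis makes no use of baseline pain, which is part of the endpoint: a small gain in precision is available, but the planned tests are valid

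*Protocol article*

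**What the plan says.** All references are to the protocol article.

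- **Endpoint** (Primary outcome): "The primary outcome is the reduction of pain in the legs 12 months after completion of liposuction", or after 12 months of CDT, with the threshold "≥ 2 points on a numerical rating scale with range 0–10; German pain questionnaire". Success is therefore defined on a change from a starting value.
- **Primary test** (Statistical methods): success "is evaluated by the stratified (by stage) Mantel-Haenszel test", "at two-sided significance level of 5% (H_0_: odds ratio = 1 vs. H_A_: odds ratio ≠ 1"). If that is significant, each stage is tested by Fisher's exact test. A missing outcome or a change of assigned treatment counts as failure.
- **Randomisation** (Patient randomisation): 2:1, stratified by stage and site. Pain is not a stratum.
- **Availability of baseline pain** (Study visits and assessments): the screening visit and later visits include "validated questionnaires for the determination of pain (German pain questionnaire"). In Tables 1 and 2 the row "Pain (German Pain questionnaire") is marked at screening, P1 and P2, and randomisation is marked at P2.
- **Entry range** (Eligibility criteria): average leg pain of 4 or more, with the criteria checked again at P2.

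No baseline-adjusted analysis of success is named. Age, centre and surgeon appear only as subgroup factors.

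**The concern.** Entry pain can lie anywhere from 4 to 10. A patient at 4 must lose half her score to succeed; a patient at 8 must lose a quarter and has more room for regression to the mean. Write X for baseline and Y for follow-up. Then cov(X, X − Y) = var(X) − cov(X, Y), which is zero only if follow-up pain rises by one full point for each baseline point. Measurement error usually pushes that slope below 1, and baseline then predicts success. Stage cannot be assumed to carry the same information, because the article defines it by skin morphology and palpation, not by pain.

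At stake is the precision of the estimated effect, and how far one stage's estimate can move because its arms happened to start at different pain levels. The stages are where this would be felt most, with about 90 versus 45 patients each.

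**Working it through.** **1. Plan's own figure.** Inputs from Determination of trial size: success "is expected to be at least 40% and that of the control to be at most 10" per cent; "The chi-square test requires 111 patients (74 vs. 37) per group to reach 80% power"; two-sided 5%; 135 per stage after inflation, which is 45 vs 90 at 2:1.

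Control patients per stage = [1.96·√(1.5·0.30·0.70) + z·√(0.10·0.90 + 0.40·0.60/2)]² / 0.30², where 0.30 in the first root is the pooled proportion (0.10 + 2·0.40)/3.

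- 80% power (z = 0.842): (1.100 + 0.386)²/0.09 = 24.5, so 25 vs 50 (75 per stage), or 30 vs 60 (90) with continuity correction.
- 90% power with continuity correction: 37 vs 74 = 111.

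So 111 does not reproduce at 80%; it matches 90% power with the correction. That is a separate matter. For this point it means only that power is higher than stated:

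- 45 vs 90 in a stage: (0.30·√45 − 1.100)/0.458 = 1.99, about 98%; Fisher's exact test by enumeration, 97%.
- 135 vs 270 overall: above 99.99%.

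**2. Size of chance imbalance.** SE of the difference in mean baseline pain, in SD units:

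- overall √(1/270 + 1/135) = 0.105
- one stage √(1/90 + 1/45) = 0.183

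With an assumed SD of 1.42 points, the 95% limits are 1.96·1.42·0.105 = 0.29 points overall and 1.96·1.42·0.183 = 0.51 points in a stage.

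**3. Gain from adjustment.** The relation between baseline and success is not in the documents, so it was varied.

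*By slope of follow-up on baseline* (assumed: integer baseline 4–10 from a rounded normal with mean 6 and SD 1.8, residual SD 1.8, 1,000 simulated trials of 405, 40% vs 10%). The unadjusted risk difference was compared with the standardised one from a logistic model with arm, stage and baseline pain. The last column is the shift from an imbalance at its 95% limit.

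| Slope | Odds ratio of success per SD of baseline, liposuction arm | SE unadjusted → adjusted | Variance reduction | Shift in percentage points: overall / one stage |
|---|---|---|---|---|
| 0.3 | 2.63 | 0.0381 → 0.0355 | 13% | 2.7 / 4.7 |
| 0.5 | 1.98 | 0.0377 → 0.0360 | 9% | 2.0 / 3.5 |
| 0.7 | 1.50 | 0.0394 → 0.0387 | 4% | 1.3 / 2.2 |
| 1.0 | 1.00 | 0.0386 → 0.0386 | 0% | 0 / 0 |

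*By correlation* (assumed: baseline mean 6.2, SD 1.4; follow-up SD 2; 3,000 trials each). Unadjusted/adjusted variance ratios for correlations 0.1 to 0.6 were 1.14, 1.15, 1.09, 1.05, 1.05 and 1.01. Two further runs gave 1.17 and 1.11 at 0.1, falling to 1.01 and about 1.00 at 0.6. The largest, 1.17, is a reduction of 1 − 1/1.17 = 14.5%. Hence roughly 0 to 15%.

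**4. Against the sampling error.** Stage-wise 95% half-width without adjustment: 1.96·√(0.24/90 + 0.09/45) = 13.4 points. With 15% less variance: 13.4·√0.85 = 12.3 points.

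**5. Power if the effect is smaller.** At 20% vs 10% overall, the Mantel-Haenszel and adjusted tests had power of 79.1% and 83.3% (slope 0.3), 81.2% and 83.5% (0.5), 74.7% and 75.3% (0.7), and 74.3% and 73.7% (1.0, no real difference).

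**The case against.** A reader might infer that leaving baseline pain out biases the primary comparison or makes the test unsafe. The documents do not support that. Randomisation makes the stage-stratified test valid, and chance imbalance in pain is already part of its 5% error rate. A reader might also infer that the trial loses power that it needs. At 40% versus 10% it does not, and a shift of 2 to 5 points lies well inside a half-width of about 13.

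The other objections are also sound:

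- The gain rests wholly on assumed inputs. The upper end needs a correlation near 0.1 to 0.2 between a patient's own pain scores a year or more apart.
- Counting missing outcomes as failures dilutes the gain. With 10% missing at random, one run gave variance ratios of about 1.04, 1.01 and 1.01 at correlations 0.4, 0.5 and 0.6.
- Adjustment is not free. A logistic odds ratio conditional on pain is a different quantity from the stage-conditional one now tested. Replacing Fisher's test by a large-sample model would be a real trade where only 0.10·45 = 4.5 control successes are expected per stage.
- Models for the secondary outcomes may properly sit in an analysis plan that is not shown, so nothing is claimed about them.

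What survives is narrow. The article fixes the primary analysis without a covariate that is already collected and is built into the endpoint, and the estimate could be somewhat sharper. The odds-ratio problem is met by standardising to a risk difference, and the small-count problem by leaving the exact tests in place.

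**Conclusion.** This is a small efficiency improvement, not an error. The planned tests hold their level and are amply powered at the planned effect. Using baseline pain would lower the variance of the risk difference by roughly 0 to 15% and remove shifts of up to about 2 to 5 percentage points in a stage's estimate. The imbalance figure takes the 95% limit and assumes that baseline predicts success (odds ratio per SD about 1.5 to 2.6); both gains vanish if follow-up pain tracks baseline one for one. A difference in power appears only if the true effect is much smaller than planned: about 4 points at most in the table of slopes, for 20% versus 10%.

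**What to change.** Keep the stage-stratified Mantel-Haenszel test and the stage-wise Fisher tests as the basis for significance. Add, before unblinding, a prespecified effect estimate: the standardised risk difference with 95% CI from a logistic model with arm, stage and pain at the last visit before randomisation (P2).

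Report it overall and, with caution because control successes are few, by stage. For the stage-wise figures, one model over all patients with an arm-by-stage term and a common pain slope avoids estimating that slope from a handful of events.

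Name the visit explicitly. The article calls screening the baseline visit, yet randomisation follows about 7 months later at P2, so the plan should also say from which visit the 2-point fall is counted.

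The cost is wording and minor programming, with no extra data or patients. The one downside is a model-based risk difference standing beside a test framed on the odds ratio; a sentence saying which serves which purpose deals with that.
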